### Participants, therapists, centres

This research will take place across six acute medical or surgical wards from Dandenong Hospital and Western Hospital (Footscray), in Victoria, Australia. Both of these hospitals are major tertiary, metropolitan hospitals. The wards (Table 1) were selected by project investigators in consultation with managers and clinicians based at each site on the basis of currently having a weekend allied health service, the patient types being treated on that ward (medical or surgical patients, not rehabilitation), and not being anticipated to undergo major structural change (for example, substantive change of patient case-mix or refurbishment requiring ward shut-down) during the study period which would confound the trial design. High-risk wards such as intensive and coronary care units, emergency departments and paediatric wards were excluded. Each hospital will commence this research at

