#### **Primary outcome measure: 1) length of stay**

Mean overall length of stay per patient who is treated on one of the targeted wards will be used as the primary outcome. This measure is often used as an indicator of hospital efficiency [26]. Length of stay is the key overall driver of inpatient costs and is the most readily available outcome to enable stopping rules to be checked during study 1. However, overall mean length of stay is limited as an outcome for this project as: i) these data can be skewed by highly influential outliers, ii) length of stay of longer-stay patients will not be known until they are

discharged (thus interim analyses for non-inferiority to check stopping rules may underestimate mean length of stay) and iii) patient admission casemix profile may vary over the study period (for example, a study ward may start admitting more patients who typically stay longer). To account for these limitations, we will also examine the proportion of patients who stay longer than their Australian Refined Diagnosis-Related Group average 'in-liner' length of stay according to data published from the previous year [27].

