patients who are exposed to both control and intervention conditions within each study will be excluded from the analyses. Analyses will be adjusted for index study ward (first study ward the patient was admitted to during that inpatient episode of care), calendar time using each step in the wedge design as a categorical covariate and for historical data collected for the outcome being examined from each site over the previous 2 years mapped against these steps to account for potential local seasonal variations in the outcomes collected.

Analyses will be conducted at a site-level with pre-planned meta-analyses across both sites using patient-level data from phase 1 and separately for phase 2. These meta-analyses will examine the main effect of the usual care weekend allied health service as opposed to the control condition across sites. A site-by-intervention interaction effect will also be examined to determine if there is heterogeneity in results between sites. This is plausible as a dose-response relationship may exist between the amount of resource allocated to the weekend allied health service and the study outcomes. In this study, local data collected prior to the study indicated that Dandenong Hospital allocated approximately four times as much resource to the acute medical and surgical wards participating in this research. Meta-regression will be employed using ward-level data, treating each ward over time as a pre-post intervention study to identify if the labour costs consumed on each ward for provision of the weekend allied health service explains variation in the change in each outcome within ward.

Patients who are exposed to both intervention and control conditions will be excluded from analyses to minimise potential contamination that is made possible by having the transition periods within the stepped wedge design.

**Study 2** These analyses will be equivalent to the analyses conducted for study 1; however, non-inferiority analyses will not be conducted for this study.

A grand meta-analysis is planned, pooling results between studies 1 and 2 to examine whether there is a significant study-by-intervention interaction effect. This analysis will examine whether the effect of the stakeholder-driven model of weekend allied health service was significantly different to that of the usual care weekend allied health service delivery model.

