#### **Deviation from registered trial protocol**

There have been two changes to the registered trial protocol. The first change was the withdrawal from both study 1 and study 2 of what was planned to be a third study site. Originally, a third site with five participating wards was planned to be involved and the appropriate ethics approval was gained. The ethics committee at this site retracted this approval due to subsequent opposition from senior medical staff. Project investigators met with these senior medical staff to discuss their concerns; however, agreement could not be reached regarding the issues raised to enable the trial to continue at this site.

The second change was that the broader health network, within which the Western Health (Footscray) site operates, decided to transfer some services from that site to another site within their network. This has resulted in only 5 wards being available to participate in study 2 at this site. This is likely to result in some changes to case-mix at the Western Health (Footscray) site during study 2. These changes are planned to take effect in early 2015 when the intervention phase of study 2 is in progress,

thus it was decided to make the changes to the study wards involved from the commencement of phase 2.

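### Case-mix is foreseen to shift, but the stated models contain no patient-level variable, leaving mean stay, readmission and adverse events open to chance confounding by ward-specific shifts

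*Protocol*

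**What the plan says.** On case-mix, the protocol makes two statements of different strength.

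- Under Primary outcome measure 1 (length of stay), the third listed limitation of mean stay is that "patient admission casemix profile may vary over the study period". The answer given there is: "To account for these limitations, we will also examine the proportion of patients who stay longer than their Australian Refined Diagnosis-Related Group average" in-liner stay.
- Under Deviation from registered trial protocol, services are to move away from the Western site in early 2015, while study 2 is running: "This is likely to result in some changes to case-mix at the Western Health (Footscray) site during study 2". The response is to settle the ward set in advance: "thus it was decided to make the changes to the study wards involved from the commencement of phase 2". Table 1 accordingly marks ward 2 W as taking part in study 1 only.

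Under Participants, therapists, centres, wards were chosen partly for "not being anticipated to undergo major structural change", with a substantive change in case-mix given as an example.

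On the model, the Statistical analysis section says: "Analyses will be adjusted for index study ward (first study ward the patient was admitted to during that inpatient episode of care"). It then adds "calendar time using each step in the wedge design as a categorical covariate", and each site's outcome history over the previous two years, mapped to the steps to allow for season. Admissions are nested in wards as random factors. Study 2 uses equivalent analyses, without non-inferiority testing. No patient characteristic is named.

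**The concern.** Each stated adjustment removes a particular kind of change. Index ward removes stable differences between wards. Step removes changes shared by all wards of a site. Site history removes recurring seasonality. None removes a new change in the patients of one ward partway through the wedge. Because one ward switches per step, such a change can be read partly as an effect of the weekend service.

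The protocol's own remedy, the AR-DRG-referenced proportion, covers one of the two length-of-stay analyses. It does not adjust mean stay, which remains a primary outcome, and it has no counterpart for readmission or adverse events.

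At stake is mainly the Western estimate in study 2. It enters the patient-level pooling across sites and the study-by-intervention test comparing the stakeholder-driven model with the usual-care model.

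**Working it through.** The protocol gives no size for any case-mix shift and no bias figure, so there is nothing of its own to reproduce. The check asks what fraction of a shift in one ward passes into the treatment estimate under the stated adjustment for ward and step.

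**Inputs**
- Western starts in April 2014 (Participants, therapists, centres) and runs 13 months in total, with 5 wards in study 2 (note on the design figure). Study 1 takes 7 months (Group 1), so study 2 has 13 - 7 = 6 months, November 2014 to April 2015.
- The transfer is dated only as early 2015. *Assumption:* February 2015, which is month 4 of study 2.
- In study 2, one ward switches on in each of months 2 to 6, in random order.
- *Assumption:* the shift starts in month 4, lasts to month 6 and is confined to one ward.

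**Formula.** With ward and step effects and equal cell sizes, the least-squares weight of a ward-month cell is r / S. Here r = x - (ward mean of x) - (month mean of x) + (overall mean of x), x is the 0/1 treatment indicator, and S is the sum of r·x over all cells. A unit shift in ward i from month 4 moves the estimate by (sum of r over months 4 to 6 in ward i) / S.

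**Numbers.** Ward means are 5/6, 4/6, 3/6, 2/6 and 1/6. Month means are 0, 0.2, 0.4, 0.6, 0.8 and 1. The overall mean is 0.5. Summing r over the treated cells gives 0.333 + 0.533 + 0.600 + 0.533 + 0.333, so S = 2.333.

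| Ward by order of switching | Sum of r, months 4-6 | Fraction of shift passed on |
|---|---|---|
| 1st | 0.067 - 0.133 - 0.333 = -0.400 | -0.17 |
| 2nd | 0.233 + 0.033 - 0.167 = 0.100 | 0.04 |
| 3rd (switches in month 4) | 0.400 + 0.200 + 0 = 0.600 | 0.26 |
| 4th | -0.433 + 0.367 + 0.167 = 0.100 | 0.04 |
| 5th | -0.267 - 0.467 + 0.333 = -0.400 | -0.17 |

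- Sum over the five positions: 0. The expected bias over random orders is zero.
- Mean absolute value: (0.171 + 0.043 + 0.257 + 0.043 + 0.171) / 5 = 0.137, about 0.14.
- A shift common to all five wards: 0, because step absorbs it.
- If the shift starts in month 3 or 5 instead, the range is -0.20 to +0.23.

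**Illustration** (the size is assumed). A 2-day shift in one ward's expected stay gives 0.137 × 2 = 0.27 day typically and 0.257 × 2 = 0.51 day in the worst position. A 5-point shift in one ward's readmission risk gives at most 0.257 × 5 = 1.3 points.

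**Study 1, for comparison.** With 6 wards and 7 steps, the range for a one-ward shift starting mid-wedge is -0.17 to +0.21. To use up the 1-day limit, one ward's expected stay would have to shift by about 1 / 0.214 = 4.7 days.

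**Precision from adjustment.** In a linear model the standard error falls by 1 - √(1 - R²). If admission covariates explain 5% to 20% of the variance (assumption), this is 1 - √0.95 = 3% to 1 - √0.80 = 11%.

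**Cost of a before/after-transfer term.** For one ward, the information on treatment falls from S to S - (sum of r)² / 1.2. The 1.2 is 3 × ½ × 4/5, the residual sum of squares of the transfer indicator. The standard error rises by √(2.333 / 2.033) - 1 = 7% for the ward switching in month 4, by √(2.333 / 2.200) - 1 = 3% for the first or last ward, and by 0.2% for the other two.

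**The case against.** The case on the other side is substantial.

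- **Safeguards exist.** Wards expected to change substantially were not selected. The Western ward set was fixed before study 2, so the loss of ward 2 W cannot act as a mid-study change. Step effects remove site-wide shifts, and a sensitivity analysis covers unit closures. All of this stands, but none of it holds the patient mix constant within the five remaining wards, where the protocol itself still calls a change likely.
- **The order is random.** A reader might infer a systematic bias towards or away from the service. The documents do not support that, because the effects sum to zero over orders. With five wards and a single realised order, however, the chance error in that order can be appreciable, and the stated model has no term for it.
- **The margin.** A reader might set 0.5 day against the 1-day limit. That limit belongs to study 1. Study 2 has no non-inferiority analysis, and for study 1 the protocol foresees no specific case-mix change.
- **General expectation.** A reader might infer that the plan expects case-mix to change throughout. The wording is that it may vary in general, and is likely to change only at Western in study 2.
- **Left to the analysis plan.** Further covariates could appear in an analysis plan that is not shown. Against that, this document names the threat, states its remedy and lists its covariates, so the choice as written can be judged.

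**Conclusion.** The point holds in a limited form. The stated covariate set contains no patient-level variable, although the protocol foresees case-mix change, and the AR-DRG measure protects only one of the length-of-stay analyses. The consequence is chance confounding in the realised order of 5 or 6 wards, with zero expectation over allocations.

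For Western study 2 the size is -0.17 to +0.26 of a one-ward shift, with a mean absolute value of 0.14. In days this is about 0.3 typically and 0.5 at worst. The day figures rest on an assumed 2-day shift from February 2015, neither of which the documents give. The figures do not show that any margin is threatened. The practical consequence is a less reliable Western estimate going into the pooled analysis and into the comparison of study 1 with study 2.

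The precision gain of 3% to 11% applies to linear models such as length of stay, given the assumed R². It should not be claimed for the binary or rate outcomes.

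**What to change.** In every primary model, add pre-specified patient variables fixed at admission: age (already needed for eligibility) and, if the administrative record holds them, sex, emergency or planned admission, and admitting unit.

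As sensitivity analyses only:
- adjust mean stay for the patient's AR-DRG average inlier stay, which the trial already needs for its other length-of-stay measure. It is kept out of the primary model because the group may be coded after exposure to the service;
- for Western study 2, add a before/after-transfer term for the wards that gain or lose services.

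The cost is a few more extracted fields and model terms. The transfer term raises the standard error of the treatment effect by about 0% to 7% when one ward is affected. For a ward that switches in the month of transfer, the term coincides with its treatment indicator, so that ward's own before/after contrast is lost. That is why it should not be in the primary model.

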## Abstract

**Background:** Disinvestment from inefficient or ineffective health services is a growing priority for health care systems. Provision of allied health services over the weekend is now commonplace despite a relative paucity of evidence supporting their provision. The relatively high cost of providing this service combined with the paucity of evidence supporting its provision makes this a potential candidate for disinvestment so that resources consumed can be used in other areas.

This study aims to determine the effectiveness, cost-effectiveness and safety of the current model of weekend allied health service and a new stakeholder-driven model of weekend allied health service delivery on acute medical and surgical wards compared to having no weekend allied health service.

**Methods/Design:** Two stepped wedge, cluster randomised trials of weekend allied health services will be conducted in six acute medical/surgical wards across two public metropolitan hospitals in Melbourne (Australia). Wards have been chosen to participate by management teams at each hospital. The allied health services to be investigated will include physiotherapy, occupational therapy, speech therapy, dietetics, social work and allied health assistants. At baseline, all wards will be receiving weekend allied health services. Study 1 intervention will be the sequential disinvestment (roll-in) of the current weekend allied health service model from each participating ward in monthly intervals and study 2 will be the roll-out of a new stakeholder-driven model of weekend allied health service delivery. The order in which weekend allied health services will be rolled in and out amongst participating wards will be determined randomly. This trial will be conducted in each of the two participating hospitals at a different time interval. Primary outcomes will be length of stay, rate of unplanned hospital readmission within 28 days and rate of adverse events. Secondary outcomes will be number of complaints and compliments, staff absenteeism, and patient discharge destination, satisfaction, and functional independence at discharge.

(Continued on next page)

\* Correspondence: [contact]

Allied Health Research Unit, Monash Health and Physiotherapy Department, Monash University, Melbourne, Victoria, Australia

Full list of author information is available at the end of the article

(Continued from previous page)

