**Table 1 Caseload in participating wards**

| Hospital           | Ward             | Description                                                         |
|--------------------|------------------|---------------------------------------------------------------------|
| Dandenong Hospital | SW3/W2 acute     | Orthopaedic surgery                                                 |
|                    | SW4              | Stroke unit                                                         |
|                    | West 3           | Thoracic, Vascular, General surgical and medical units              |
|                    | West 4           | General medicine                                                    |
|                    | North Ward       | Head and neck, Plastics                                             |
|                    | North 3          | Surgical                                                            |
| Western Hospital   | 2B               | Medical                                                             |
|                    | 2C               | Medical                                                             |
|                    | 2D               | Infectious diseases; Respiratory medicine                           |
|                    | 2 W a | Plastics; Head and neck surgery; ENT surgery                        |
|                    | 3 W              | General surgery; Colorectal; Breast; Endocrine; Urology             |
|                    | 3E               | General surgery; Vascular surgery; Thoracic; Upper gastrointestinal |

aStudy 1 only.

different time points (Dandenong Hospital commencing February 2014 and Western Hospital (Footscray) commencing April 2014).

Data in this study will be collected from three groups of participants. Each group of participants is now described in detail.

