#### **Group 1**

'All patients on participating wards.' This group will consist of patients admitted to acute medical or surgical wards involved in the trial who are over the age of 18 years. Paediatric patients will be excluded from this study as they are not routinely seen on the selected wards (none are paediatric units or have paediatric beds) and have different provisions for service delivery. It is anticipated, based on previous patient flow data, that each ward will have an average of 174 patient admissions per month during the trial. This means that 6 wards at 1 site will have 7,308 patient admissions during the 7 months of study 1 and 7,308 during the 7 months of study 2. This will lead to an anticipated total of 29,232 patient admissions during the overall study period.

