### **Randomisation and allocation concealment**

The order in which weekend allied health services will be rolled in and out from each participating ward will be determined at random by an investigator blinded to ward identity. One investigator will develop pseudonyms for each ward while another investigator blinded to the true identity of each pseudonym will use a random number generator in Microsoft Excel (Microsoft Corporation, Redmond, WA, USA) to allocate ward number locations to each pseudonym. The first investigator will then be able to reveal which pseudonym represented which ward.

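### The dose-response meta-regression uses each ward's pre-post change, so time patterns and other hospital differences can enter the labour-cost slope

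*Protocol*

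**What the plan says.** In the Study 1 part of the protocol's Statistical analysis section, the main comparison is a patient-level mixed model. The text says in general terms that analyses will be adjusted for index ward, for "calendar time using each step in the wedge design as a categorical covariate", and for each site's outcome data from the previous two years, mapped to the steps to allow for local seasonal variation.

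The next paragraph raises a possible dose-response relationship and reports that "Dandenong Hospital allocated approximately four times as much resource to the acute medical and surgical wards participating in this research". It then specifies a meta-regression on ward-level data, "treating each ward over time as a pre-post intervention study to identify if the labour costs consumed on each ward" for the weekend service "explains variation in the change in each outcome within ward". It names no concurrent comparison, calendar term or site term for this analysis. Study 2 analyses are to be equivalent, apart from non-inferiority.

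On timing, the text around Table 1 has "Dandenong Hospital commencing February 2014 and Western Hospital (Footscray) commencing April 2014". The Group 1 section gives six wards per site and seven months for Study 1. The abstract describes withdrawal ward by ward in monthly intervals.

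**The concern.** A stepped wedge separates the service effect from calendar time because, in most months, some wards have the service and others do not. Reducing each ward to one pre-post change removes that comparison, so the change contains whatever else moved between the ward's early and late months.

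This would matter little for a cost slope if it added the same amount to every ward. It may not. The two hospitals occupy calendar windows two months apart, and they sit at opposite ends of the cost scale. A time pattern that shifts their pre-post changes by different amounts is therefore aligned with cost and can appear as a cost effect. The same holds for any other hospital difference in how outcomes changed.

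At stake is the reading of the protocol's named ward-level test of whether resource explains effect, in a trial about disinvestment.

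**Working it through.** The protocol states no power, error rate or expected slope for the meta-regression, so there is no figure to reproduce. The check asks what pre-post changes would appear with no service effect at all.

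**Inputs from the protocol**
- Six wards per site, seven months: "6 wards at 1 site will have 7,308 patient admissions during the 7 months of study 1".
- Monthly steps: "sequential disinvestment (roll-in) of the current weekend allied health service model from each participating ward in monthly intervals".
- Windows: February to August (Dandenong) and April to October (Western), with five months shared.
- Cost ratio of about 4:1. Ward order is random.

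**Assumptions, not in the documents**
- An annual cosine of amplitude A, with the peak month p varied over the year.
- A within-site coefficient of variation (CV) of cost from 0 to 0.5.

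**Formula.** The ward crossing after month k (k = 1 to 6) has change = mean(months k+1 to 7) - mean(months 1 to k).

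**Step 1: linear trend.** With slope b per month, the change is b[(k+8)/2 - (k+1)/2] = 3.5b for every k and for either start month. A linear trend common to both sites therefore goes into the intercept and leaves the cost slope alone.

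**Step 2: season, July peak.** Let s(m) = A cos(2π(m-7)/12). February to October then take the values -0.866, -0.5, 0, 0.5, 0.866, 1, 0.866, 0.5, 0 (times A). For k = 1:
- Dandenong: (-0.5 + 0 + 0.5 + 0.866 + 1 + 0.866)/6 - (-0.866) = 0.455 + 0.866 = 1.32A.
- Western: (0.5 + 0.866 + 1 + 0.866 + 0.5 + 0)/6 - 0 = 0.62A.

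| k | 1 | 2 | 3 | 4 | 5 | 6 | Mean |
|---|---|---|---|---|---|---|---|
| Dandenong (×A) | 1.32 | 1.33 | 1.26 | 1.13 | 0.93 | 0.70 | 1.11 |
| Western (×A) | 0.62 | 0.40 | 0.14 | -0.14 | -0.40 | -0.62 | 0.00 |

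**Step 3: other peak months.** Gap in mean change, Dandenong minus Western:

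| Peak | Mar | Apr | May | Jun | Jul | Aug | Sep |
|---|---|---|---|---|---|---|---|
| Gap (×A) | 0 | 0.64 | 1.11 | 1.28 | 1.11 | 0.64 | 0 |

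Peaks from October to February give -0.64, -1.11, -1.28, -1.11 and -0.64. The range is -1.28A to +1.28A.

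**Step 4: effect on the cost slope.** The 12 ward changes were regressed on cost. Site means were 4 and 1, ward order was random, there were 4,000 draws, and the peak was placed at month 7.5, where the gap is 0.91A. The contrast is 4 - 1 = 3 cost units.

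| Within-site CV of cost | 0 | 0.25 | 0.5 |
|---|---|---|---|
| Share of cost variance explained by site | 100% | 85% | 61% |
| False change across the fourfold contrast, no site term | 0.91A | 0.78A | 0.60A |
| False slope per cost unit, with site term | not estimable | -0.001A | 0.001A |

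With a site term the false slope vanishes on average, because ward order is random within site.

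**The case against.** The strongest reply is that the same section says analyses will be adjusted for step and for two years of site-specific history, expressly because of season. A reader might infer that the meta-regression has no seasonal adjustment. The protocol does not say that; it leaves open whether and how the adjustment applies. If each ward's change were corrected by its site's historical pattern, much of a recurring seasonal bias would go. Two things remain. A categorical step term does not fit a regression with one change per ward. And past years cannot remove a pattern specific to the trial period, or a hospital difference that is not seasonal.

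A reader might also take the July figure, set A at one percentage point, and compare the 1.1-point gap with the 2-point margin in the Trial safety section. That is not supported. The amplitude and peak are assumptions, the gap is zero for a March or September peak and negative from October to February, and that margin belongs to stopping rules for the difference between no service and service. No decision rule rests on the meta-regression.

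Nor is the slope shown to be only a two-hospital contrast. Table 2 (Item 8) says service hours also vary between wards within each site, the windows share five of seven months, and "The order in which weekend allied health services will be rolled in and out from each participating ward will be determined at random". The confounding is partial, and its degree cannot be fixed from the protocol.

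Finally, covariates for an explanatory analysis may be left to an analysis plan. That is fair for the covariates, but the pre-post form is fixed in the protocol itself.

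**Conclusion.** The point holds in a limited form. The protocol fixes a pre-post ward-level analysis that discards concurrent wards, and it relates the result to a cost variable partly aligned with hospital. A non-linear or site-specific time pattern can then enter the cost slope; a linear trend common to both sites cannot.

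Under an assumed annual cosine with no seasonal correction, the false between-site gap is anywhere from -1.28A to +1.28A. At A = 1 percentage point (an illustration only) that is -1.28 to +1.28 points, so the sign as well as the size is unknown.

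The broader weakness does not depend on season: with two hospitals, the between-site part of the slope cannot be told apart from anything else that differs between them. The main intervention-versus-control estimate is not affected. The protocol should be changed here, but this is not a threat to the trial's primary conclusions.

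**What to change.** Replace the pre-post meta-regression with a service-by-labour-cost term in the patient-level stepped-wedge model already planned. Use site-specific step effects, because step 1 is February at one hospital and April at the other. An alternative is to take ward-specific service effects from that model and relate those to cost.

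In either case, split labour cost into the site mean and the ward's deviation from it, and report the two associations separately. Describe the between-site part as not separable from other hospital differences. State how the two-year historical adjustment enters this analysis.

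The cost is a change of wording and one different model on the same data. The within-site slope rests on six wards per site in Study 1 and will be less precise. The fourfold contrast that motivates the dose-response question is still reported, as a descriptive between-hospital comparison.
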